#### Sample size

The sample size calculation for this study is based on the linear mixed model that will be adopted to answer research questions 1 and 2 based on the repeated ecological momentary assessment data from the intervention and control group and the effect size of 0.29 from previous studies (unpublished manuscript). The R package *sjstas* [44], and *pwr* [45] were used for sample size calculation. The results indicate that a total of 536 participants will be required to detect a significant difference at an alpha level of 0.05 and a power of 80%. Accounting for potential dropouts, we conservatively estimate that 20% of participants may not complete the study. Therefore, we plan to recruit 670 participants (335 in each group).

#### Recruitment

Mass emails will be sent to organizations about children with ASD to attract parents interested in the study. Also, online recruitment advertisements will be posted on different online discussion boards. Voluntary participants can directly contact our recruitment staff via telephone, email, or by submitting the online application form for a subsequent briefing meeting. After the briefing session, participants’ consent will be obtained.

#### Randomization and allocation

Individual randomization by a serially numbered opaque sealed envelope (SNOSE) will be used to ensure the allocation sequence was concealed from research assistants and participants before the group allocation. The principal investigator (PI) will prepare about 200 identical, opaque, sealed A5-sized envelopes, with a unique three-digit serial number on the cover of each envelope as an identifier. Half of the envelopes contain an action plan for the intervention group, and the remaining half contains an action plan for the control group. After inserting the intervention materials in the envelopes, they will be sealed, shuffled, and then numbered. When the participant consents to participate, the research assistant opens one envelope according to the serial number sequence and assigns the participant to a treatment condition based on the action plan. All the participants will not be blinded to the given interventions. Outcome assessors (research assistants) are blinded to the group allocation at the telephone follow-up.

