## Methods

### Trial design

This research adopts a parallel-armed, randomized controlled trial (RCT) design. The intervention group will receive a combination of (1) a time-based system-triggered EMA, which will collect participants’ sources and status of depression, anxiety, and depression in daily life; (2) EMI-delivered MBI, and (3) a follow-up survey of long-term effects of EMI/A-MBI. The participants will complete a baseline questionnaire and then participate in EMI via a smartphone application (App) for eight consecutive weeks and receive the daily exercise prompts. The EMA will include questions about self-reported depression, anxiety, and depression. After the 8-week EMI/A-MBI, the participants will be invited to complete a post-experimental survey with similar questions in the baseline questionnaire. Two months after completing the EMI/A-MBI, participants will be contacted to complete a telephone follow-up survey with similar questions in the baseline questionnaire. The control group will receive the longitudinal survey exactly the same as the intervention group and 8-week mindfulness-based short messages sent by the research team on a daily basis. The messages will contain audio-based instructions for mindfulness-based practice, which will be the same as the intervention group. The SPIRIT schedule of enrolment, interventions, and assessments can be found in Fig 1 and the flowchart of the design can be found in Fig 2. (The SPIRIT checklist can be found in S1 File).

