**Fig 3 pone.0291168.g003:**
[figure not shown]
Summarizations of measurements.

*The cognitive Appraisal of Health Scale* will be used to measure participants’ cognitive appraisal of daily life events. This scale includes 28 items rated from 1 strongly disagree to 5 strongly agree. This scale was developed based on the transactional theory of stress and coping and thus consists of subscales of primary appraisal (threat, challenge, harm/loss, and benign/irrelevant) and secondary appraisal. The internal consistencies were all greater than 0.70 [46].

*The Five Facet Mindfulness Questionnaire (FFMQ)-short version* [47, 48] will be used to measure participants’ level of mindfulness before and after practicing. It includes 15 items measuring the five facets of mindfulness: observing, describing, acting with awareness, non-judging of inner experience, and non-reactivity to inner experience. This scale was further validated [49] and yielded good convergent validity and internal consistency [49].

Parents’ psychological distress will be assessed in the domains of depression, anxiety, stress, and mental well-being, indicating participants’ life satisfaction and empowerment.

*The Depression Anxiety Stress Scale (DASS)* [50] is a self-report questionnaire that measures the emotional states of depression, anxiety, and stress. This scale contains 21 questions rated from 0 (did not apply to me at all) to 3 (applied to me very much, or most of the time). There were seven questions for each sub-scale of stress, depression, and anxiety [51]. This scale was reliable (alpha = 0.96 and 0.80 for the depression and anxiety subscales, respectively). Cronbach’s alpha was high for the three subscales in parents of children with ASD: 0.91 for stress, 0.87 for anxiety, 0.94 for depression, and 0.92 for full scale [51]. It has also been validated in the Hong Kong population [52].

*Satisfaction with Life Scale (SWLS)* [53]. The SWLS has five items scored on a 7-point scale (1 = strongly disagree to 7 = strongly agree) measuring participants’ satisfaction with life and has a Cronbach’s alpha for internal consistency of 0.87 and a test-retest correlation of 0.82 [53]. This scale has also been validated in Chinese [54] and Hong Kong populations [55].

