### Data analysis

Data analysis will be conducted using STATA 17 [60]. All significance tests were two-sided with a 5% level of significance. Missing data will be calculated using intention-to-treat approach. Participants who failed to answer the prompted questions will be treat as no improvement on the outcomes. The characteristics of the observed data and the missing data will be compared to determine whether there are any systematic differences. If tested that the missing data will be missing not at random, imputation methods, such as multiple imputation (MI) or maximum likelihood estimation (MLE), will be adopted to estimate the missing values based on the observed data and the relationships between variables. Moreover, sensitivity analysis will be adopted to assess the impact of the missing data on the study results and to determine the robustness of the findings. Complete case analysis and multiple imputation will also be conducted as sensitivity analysis. The internal consistency of the constructs for mindfulness, depression, anxiety, stress, and life satisfaction will be assessed with Cronbach’s alpha. In each construct, the PI will sum all items to build the score for that attribute in each participant.

To answer the first and second questions, first of all, the effect size (Heges’ g) of the outcome for both the intervention and control groups will be calculated. Subgroup analysis will be conducted when necessary. Next, linear mixed models will be conducted to compare the effectiveness of the mindfulness intervention between the two treatment groups. Linear mixed models are particularly suitable for analyzing data collected via ecological momentary assessment, as they can account for the nested and repeated nature of the data. The main predictor variable will be the treatment group (intervention vs. control), and the model will also include baseline DASS scores and any relevant demographic variables (e.g., age, gender) as covariates. The linear mixed model will include random intercepts and slopes for each participant to account for individual differences in the baseline scores and the rate of change in scores over time. The treatment group effect will be assessed using a fixed effect, and the model will also include an interaction term between treatment group and time to investigate any differential effects of the intervention over time.

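### Consent is the only stated trigger for opening the envelope, so the self-reported baseline DASS may be answered with the arm already known

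*Protocol article*

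**What the plan says.** Recruitment puts consent straight after the briefing: "After the briefing session, participants’ consent will be obtained". Participants describes the same step from explanation to consent. Neither section mentions a measurement.

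Randomization and allocation then gives the operating rule: "When the participant consents to participate, the research assistant opens one envelope according to the serial number sequence". In the same sentence the research assistant "assigns the participant to a treatment condition based on the action plan". The section adds: "All the participants will not be blinded to the given interventions".

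Trial design is the only visible text that orders the baseline questionnaire against anything else: "The participants will complete a baseline questionnaire and then participate in EMI via a smartphone application (App) for eight consecutive weeks". It does not mention the envelope.

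Among the measures listed under Outcomes, the DASS "is a self-report questionnaire that measures the emotional states of depression, anxiety, and stress". It is the primary outcome. For the linear mixed model comparing the arms, Data analysis says "the model will also include baseline DASS scores" as covariates.

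**The concern.** A baseline covariate is safe to adjust for because randomisation cannot have affected it. That holds by design only when the measurement is complete before the participant knows the allocation. Here the rule tells the research assistant to act on consent, and completion of the baseline is not a condition.

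The two arms are easy to tell apart: an app with a chatbot, library and weekly session on one side, audio instructions on the other. A parent who is pleased or disappointed by the allocation may rate current distress differently. Two things are then at stake. The adjusted group effect on the primary outcome could be displaced by a reporting difference unrelated to treatment. And some parents could withdraw between allocation and baseline because of their arm, leaving randomised people with no baseline data.

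**Working it through.** **Order of events.** The visible text gives two separate chains.

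- Recruitment with Randomization and allocation: briefing → consent → envelope → arm assigned.
- Trial design: baseline questionnaire → eight-week app phase.

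Nothing links the baseline questionnaire to the envelope. Two sequences fit the text:

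- (a) consent → baseline → envelope → app;
- (b) consent → envelope → baseline → app.

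Sequence (a) is sound. Sequence (b) is what results if the research assistant acts on the stated trigger as soon as it occurs. The rule therefore permits (b) without prescribing it.

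**Effect on the adjusted comparison.** The protocol states no figure on this point, so there is none to reproduce. For a simple baseline-adjusted comparison, with X the reported baseline, Y the outcome, b the baseline slope, and 1 and 0 the intervention and control arms:

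adjusted effect = (mean Y1 − mean Y0) − b × (mean X1 − mean X0).

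If X is measured before allocation is known, the expected baseline difference is zero. If knowing the arm shifts reported baseline by s (intervention minus control) and leaves reporting of Y unchanged, the adjusted effect moves by −b × s, a displacement of b × |s|. Higher DASS means more distress. A negative s would therefore make the intervention look less effective, and a positive s more effective. The documents do not indicate which.

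Illustration in SD units. Both b and s are assumptions; neither is in the documents.

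| b | s = 0 | s = 0.05 | s = 0.10 | s = 0.20 |
|---|---|---|---|---|
| 0.4 | 0 | 0.020 | 0.040 | 0.080 |
| 0.5 | 0 | 0.025 | 0.050 | 0.100 |
| 0.6 | 0 | 0.030 | 0.060 | 0.120 |
| 0.7 | 0 | 0.035 | 0.070 | 0.140 |

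**Which coefficient moves.** Write the model mean as a + bX + gG + cT + d(G × T), with G the arm and T time. If the recorded baseline is X* = X + sG, substituting X = X* − sG turns g into g − bs and leaves d as it was. So the group main effect is displaced and the group-by-time coefficient is not, provided baseline enters only as a main-effect covariate, as Data analysis describes it.

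**Loss before baseline.** Outcomes says demographic questions are asked only at baseline. Someone who leaves after assignment but before baseline would have neither a baseline DASS nor demographic covariates from the questionnaire. Sample size allows 20% for dropout overall and does not divide it by arm or by time, so the number of such losses cannot be estimated.

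**The case against.** The strongest reply is that the protocol never says baseline follows allocation. The trigger sentence can be read as limiting allocation to people who have consented, without excluding a step in between. Fig 1 (the SPIRIT schedule) and Fig 2 (the flowchart) are the natural places for the sequence, and the approved protocol is a supplementary file; none of these is shown. This stands. A reader might infer that the trial has chosen to allocate before baseline, and the documents do not support that. What remains is that the one written instruction for opening the envelope names consent alone.

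A second reply concerns size. It is tempting to divide the illustration by the planning effect of 0.29 and report a distortion of up to 0.14/0.29 = 48%. That figure takes the top of two assumed ranges. A shift of zero is plausible: both arms receive mindfulness content, and Blinding says the study purpose is masked. Masking the purpose does not hide the arm, but it may soften any reaction to it. The percentage is not a finding, and the displacement does not reach the group-by-time term.

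A third reply concerns attrition. A reader might infer that people lost before baseline drop out of the analysis and break the randomised comparison. Data analysis commits to intention-to-treat, a comparison of observed with missing data, multiple imputation or maximum likelihood, and sensitivity analyses; it does not state that such people are excluded. Nor does any text show that arm-related loss will occur. The narrower point stands: these provisions would have very little information to work with for a person who has no baseline record.

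**Conclusion.** The point holds as a weakness in a stated rule, not as a demonstrated error of sequence. Consent is the only written condition for opening the envelope, and no visible text requires a completed baseline first. Because participants are unblinded, the DASS is self-reported and its baseline value is a covariate, the rule allows a post-allocation measurement to enter the primary comparison and allows loss before baseline.

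The documents do not determine the size or direction of any bias. In the illustration it runs from 0 to 0.14 SD in the baseline-adjusted group effect. That rests on an assumed slope of 0.4 to 0.7, an assumed shift of 0 to 0.20 SD, no matching shift at follow-up, and baseline entering as a main effect only. The conclusion is conditional on Figs 1 and 2: if they show baseline before allocation, what is left is a wording correction. It is worth making in either case, because analysis cannot reliably undo a baseline collected after the arm is known.

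**What to change.** Amend Randomization and allocation to say that the research assistant opens the next envelope only after the participant has consented and the baseline questionnaire has been submitted and time-stamped. If Figs 1 and 2 already show that order, this brings the text into line with them; if they show another order, change them too.

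The cost is one sentence. The sample size, measures and analysis model stay as they are, and no extra data items are needed beyond the time stamp. People who consent but do not complete the baseline would then not be randomised and would be counted as such in the participant flow.

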#### Blinding

Although it is not possible to blind the participants to group allocation for psychological interventions, the study purpose will be masked to participants. The study statistician will also be blinded to the group allocation, and participants’ personal identifiers will not be included in the dataset.

#### Intervention description

*EMI/A-MBI app*. The EMI/A-MBI app will include five main parts: a virtual counselor (a chatbot with pre-set algorism for responding to participants), an intervention library, weekly mindfulness practice, an assessment bank, and a daily emotion log. In the eight weeks, the virtual counselor in the chatbot will initiate the conversation every day three times (morning, afternoon, and evening) to check the status of the participants. If the participants responded, the virtual counselor would invite them to rate their depression, stress, and anxiety and then recommend appropriate mindfulness practices in the intervention library, such as 3-minute breathing space or mindful eating. The conversation between the virtual counselor and participants will be in the format of a menu list, and participants can easily choose from different options. After the participants finish the mindfulness practice, the virtual counselor will check the participants’ mental health status again. Suppose the participants do not respond to the virtual counselor for the whole day. In that case, the EMI/A-MBI app will prompt a short survey for psychological distress from the assessment bank and recommend mindfulness practice at the end of the day. Participants can also initiate the conversation with the virtual counselor at any time of the day, and the process will be the same. The participants can also go to the intervention library to find the mindfulness practice they prefer. The intervention library will include audio and videos of different mindfulness exercises, such as mindful walking, mindful yoga, or loving and kindness mindfulness. (Example description of the mindfulness practice can be found in S1 Table). Scripts of the audio and videos will also be provided in the intervention library. The daily emotion log will be prompted to the participants every morning since the second day of the intervention as a visual aid for participants to be aware of the change in their psychological distress and mental well-being. Every Saturday, the app will prompt reminders for the participants to join the formal 2.5-hour mindfulness practice. (The App design can be found in S2 File).

#### The control condition

To control for attention, placebo effects, and the social desirability effect, each participant in the control group will receive three mindfulness practice reminders with audio-recorded instructions on how to practice mindfulness (Audio-Mindfulness). The contents of the audio-recorded mindfulness instructions will be adapted in this study to fit parents of children with autism.

#### The explanation for the choice of comparators

As mindfulness-based intervention has been proven effective for parents of children with autism, we will involve the components of mindfulness in both the intervention and control groups. Therefore, any extra effects incurred in the intervention group can be attributed to the benefits of using EMI and EMA.

The intervention will be discontinued or modified when participants report feeling more psychological distress while practicing mindfulness-based intervention.

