**Method:**

The proposed study will recruit 670 parents of children with ASD and randomly assign them to the intervention and control groups (335 in each group). Participants in the intervention group will install the EMI/A app on their smartphones. In the app, participants can receive practice prompts daily, browse and practice different mindfulness exercises in the intervention library at any time, talk to a virtual counselor (chatbot) when feeling stressed, complete EMA on the cognitive appraisal of life events, and receive the log of change of psychological status daily. Participants in the control group will only receive audio-based standardized mindfulness practice instructions three times per week. The effects of MBI will be assessed based on the EMA data, right after the intervention and at the 2-month follow-up. The primary outcome will be participants’ psychological distress measured by the depression anxiety stress scale. The secondary outcomes will include participants’ subjective well-being, measured by the satisfaction with life scale, and level of resilience, measured by the psychological empowerment scale. Multilevel structural equational modelling will be applied to examine the pathways of the relationship between daily life events, cognitive appraisal, and psychological distress.

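### The control arm's mindfulness schedule is stated in conflicting ways, and the credit given to EMI and EMA overlooks a weekly 2.5-hour practice described only for the app arm

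*Protocol article*

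**What the plan says.** The control schedule appears in three places in the protocol article.

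- Abstract, Method: "Participants in the control group will only receive audio-based standardized mindfulness practice instructions three times per week".
- Methods, Trial design: controls receive "8-week mindfulness-based short messages sent by the research team on a daily basis". The next sentence adds that the audio instructions are the same as in the intervention group.
- The control condition: "each participant in the control group will receive three mindfulness practice reminders with audio-recorded instructions on how to practice mindfulness". No period is attached to the number.

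For the app arm, Intervention description lists among the main parts of the app "an intervention library, weekly mindfulness practice, an assessment bank, and a daily emotion log". The chatbot opens a conversation three times a day. The same section adds: "Every Saturday, the app will prompt reminders for the participants to join the formal 2.5-hour mindfulness practice".

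The explanation for the choice of comparators says "we will involve the components of mindfulness in both the intervention and control groups" and draws from this that "any extra effects incurred in the intervention group can be attributed to the benefits of using EMI and EMA".

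**The concern.** There are two linked problems.

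First, the frequency of the control intervention is contradictory. Three times per week and daily cannot both be right, and the section that defines the control condition gives a bare number that fits either a weekly or a daily reading. A reader cannot tell what dose the app is being compared with.

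Second, the attribution does not follow from its premise. Having mindfulness in both arms isolates the delivery mode only if the mindfulness dose is also common to both. The weekly formal practice is described for app users alone, so the arms differ in the amount and format of mindfulness practice as well as in momentary delivery and assessment. If the app arm does better, the result could be reported as evidence for EMI and EMA when part of it came from long formal sessions.

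**Working it through.** The article states no total dose for either arm, so there is no figure to reproduce. The check multiplies out the stated frequencies and then sets the two arms side by side.

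**Inputs**

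- Duration: 8 consecutive weeks (Trial design), i.e. 7 × 8 = 56 days and 8 Saturdays.
- Control frequency: 3 per week (Abstract); daily (Trial design); three, no period (The control condition).
- App arm: three chatbot-initiated contacts per day and one prompted 2.5-hour practice each Saturday (Intervention description).

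**Control messages over 8 weeks**

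| Reading | Calculation | Messages |
|---|---|---|
| Abstract | 3 × 8 | 24 |
| Trial design, assuming one message per day | 7 × 8 | 56 |
| The control condition, if three means per day (assumption) | 3 × 7 × 8 | 168 |

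The conflict between the Abstract and Trial design is 56 − 24 = 32 messages, or 56/24 = 2.33-fold. The third row shows only what the missing period leaves open (168/24 = 7-fold). No section states a per-day figure of three for controls.

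**Formal practice over 8 weeks**

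- App arm, all sessions attended: 8 × 2.5 h = 20 h. This is a maximum, because the app only prompts users to join.
- At assumed attendance of 50%: 0.50 × 20 = 10 h. At 25%: 0.25 × 20 = 5 h. The article gives no attendance rate.
- Control arm: none described.

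**Does the attribution follow?**

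1. The premise is that mindfulness components are in both arms.
2. The conclusion is that any extra effect belongs to EMI and EMA.
3. Getting from the first to the second requires that nothing else relevant to mindfulness differs between arms.
4. The statement in Trial design that the audio is the same covers content. It does not cover frequency or the Saturday practice.
5. The Abstract limits controls to the audio instructions, and the section on concomitant care asks participants to avoid mindfulness practice from outside the study, so controls should not obtain an equivalent session elsewhere.
6. At any non-zero Saturday attendance the arms therefore differ in practice dose as described, and the third step fails.

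**The case against.** The strongest reply is that the weekly practice is itself one of the app's five parts. On that view, using EMI and EMA simply means receiving the app as built, and extra practice prompted by the app is part of how it works rather than a confounder. The aims and hypotheses compare intervention with control at that level, and that comparison is unaffected. This much stands: a package reading is possible and would be sound. But the rationale does not say so. It reasons from mindfulness being shared between arms, and a formal 2.5-hour session is mindfulness content that, on the text, is not shared.

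Other points on that side have some weight:

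- The restriction on outside practice applies to both arms and does not stop controls replaying the study audio. That is true, so it bars an equivalent outside session but not extra use of supplied material.
- The figure of 168 messages and the attendance rates are assumptions, and none of the dose figures translates into an effect on the distress score. That is also true; they show the range left open, not a bias estimate.
- The schedule figure, the app design file and the approved protocol are not shown and may settle the control schedule. They may, but two incompatible frequencies in current text are a misstatement rather than condensation.
- Letting the Abstract override the Methods text is a guess. This is fair, which is why the approved protocol should decide.

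**Conclusion.** The concern holds on both counts and should be fixed. The control schedule is contradictory: 24 versus 56 messages over 8 weeks, taking daily as one per day, and the section defining the control condition does not resolve it. The attribution of any extra effect to EMI and EMA is unsupported as worded, because up to 20 hours of formal practice is described for the app arm and none for controls. The contradiction rests on the text alone. The attribution point rests on the text shown describing no weekly formal practice for controls, which the Abstract's restriction of controls to audio instructions supports. Neither point undermines the randomised comparison of the app package with audio messages. What is lost is a clear definition of the comparator and the narrower causal claim.

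**What to change.** Before enrolment:

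1. Check the intended control schedule against the approved protocol (S3 File) and state it, with its period, identically in the Abstract, Trial design and The control condition. Unless the approved protocol says otherwise, use three times per week for 8 weeks (24 messages), as in the Abstract and compatible with the three reminders in The control condition, and correct the daily wording in Trial design.
2. Reword the conclusion in the explanation for the choice of comparators along these lines: any group difference will be attributed to the EMI/A-MBI app package as a whole, including the weekly formal practice, compared with audio mindfulness messages.

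The cost is wording in Trial design, The control condition and the comparator rationale; in the Abstract only if the approved schedule differs from it; and in the consent text if it states the control schedule. The price is a narrower claim, about the package rather than EMI and EMA alone. Offering the weekly practice to both arms would remove this dose difference, but it would change the control arm and is not recommended here.
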